## Abstract

**Background:**

The Center for Disease Control and Prevention’s Stopping Elderly Accidents, Deaths, and Injuries (STEADI) initiative offers health care providers tools and resources to assist with fall risk screening and multifactorial fall risk assessment and interventions. Its effectiveness has never been evaluated in a randomized trial.

**Objective:**

This study aims to describe the protocol for the STEADI Options Randomized Quality Improvement Trial (RQIT), which was designed to evaluate the impact on falls and all-cause health expenditures of a telemedicine-based form of STEADI implemented among older adults aged 65 years and older, within a primary care setting.

**Methods:**

STEADI Options was a pragmatic RQIT implemented within a health system comparing a telemedicine version of the STEADI fall risk assessment to the standard of care (SOC). Before screening, we randomized all eligible patients in participating clinics into the STEADI arm or SOC arm based on their scheduled provider. All received the Stay Independent screener (SIS) to determine fall risk. Patients were considered at risk for falls if they scored 4 or more on the SIS or answered affirmatively to any 1 of the 3 key questions within the SIS. Patients screened at risk for falls and randomized to the STEADI arm were offered a registered nurse (RN)–led STEADI assessment through telemedicine; the RN provided assessment results and recommendations to the providers, who were advised to discuss fall-prevention strategies with their patients. Patients screened at risk for falls and randomized to the SOC arm were asked to participate in study data collection only. Data on recruitment, STEADI assessments, use of recommended prevention services, medications, and fall occurrences were collected using electronic health records and patient surveys. Using staff time diaries and administrative records, the study prospectively collected data on STEADI implementation costs and all-cause outpatient and inpatient charges incurred over the year following enrollment.

**Results:**

The study enrolled 720 patients (n=307, 42.6% STEADI arm; n=353, 49% SOC arm; and n=60, 8.3% discontinued arm) from September 2020 to December 2021. Follow-up data collection was completed in January 2023. As of February 2024, data analysis is complete, and results are expected to be published by the end of 2025.

**Conclusions:**

The STEADI RQIT evaluates the impact of a telemedicine-based, STEADI-based fall risk assessment on falls and all-cause health expenditures and can provide information on the intervention’s effectiveness and cost-effectiveness.

**Trial Registration:**

ClinicalTrials.gov NCT05390736, http://clinicaltrials.gov/ct2/show/NCT05390736

**International Registered Report Identifier (IRRID):**

RR1-10.2196/54395

## Introduction

Falls were the leading cause of nonfatal injuries and the leading cause of unintentional injury-related deaths among older adults (aged ≥65 years) in the United States in 2020, resulting in approximately 37,000 deaths, 3 million emergency department visits, and 1 million hospitalizations [1]. Falls among older adults are expensive, resulting in US medical costs of US $50 billion in 2015 [2]. With the aging population, the burden of falls on health care systems will continue to rise if fall prevention efforts are not expanded in clinical settings [3]. In a systematic review, Gillespie et al [4] found that multifactorial interventions significantly reduced the rate of falling among community-dwelling older adults. In more recent years, digital and telehealth programs for older adults have been implemented to evaluate their effectiveness in improving overall health and fall prevention [5-7].

The Stopping Elderly Accidents, Deaths, and Injuries (STEADI) initiative, developed by the US Centers for Disease Control and Prevention (CDC), offers health care providers tools and resources to assist with fall risk screening and multifactorial fall risk assessment and interventions [8]. The core components of STEADI are to screen, assess, and intervene: (1) screen older adults for fall risk using the 3 key questions (Have you fallen in the past year? Do you feel unsteady when walking or standing? and Do you have a fear of falling?) or the CDC’s Stay Independent screener (SIS) to identify patients at risk of falls [9]; (2) assess those who screened at risk for modifiable risk factors including gait and balance disturbances, medication risk, home hazards, orthostatic blood pressure, vision changes, concerns about feet and footwear, need for vitamin D supplementation, and comorbidities that increase fall risk [10]; and (3) intervene with evidence-based clinical and community strategies to reduce fall risk by addressing modifiable risk factors identified during the assessment [11,12]. STEADI has been implemented in full in primary care settings and in abbreviated versions in pharmacy and inpatient settings [9,13,14].

Evaluations of STEADI’s impact on outcomes has been limited. In a previous implementation of abbreviated STEADI in community pharmacies, Blalock et al [13] conducted a randomized controlled trial that compared the fall reduction impact of a pharmacist-led abbreviated medication management assessment implemented in 65 community pharmacies in North Carolina and usual care. The intervention successfully identified medication risks but found no statistically significant differences between the intervention and usual care groups in subsequent prescribing or fall outcomes during the observation period.

A recent multicenter clinical fall prevention study, the Strategies to Reduce Injuries and Develop Confidence in Elders (STRIDE), implemented a cluster-randomized trial of a nurse-administered multifactorial intervention in 86 primary care practices. The study compared the effects of a multifactorial intervention targeting modifiable risk factors to enhanced usual care [15]. They found that the intervention resulted in a significantly lower rate of a first self-reported fall injury compared to enhanced usual care, but no significant differences in rates of a first adjudicated serious fall injury, hospitalization, or death were found between the 2 groups [15]. Additional efforts are needed to evaluate the impact of clinical fall prevention on various health outcomes in clinical settings, including through telemedicine.

This paper describes the implementation protocol of the STEADI Options Randomized Quality Improvement Trial (RQIT) as implemented through telemedicine in primary care clinics to reduce falls among community-dwelling older adults. We designed the STEADI Options RQIT to estimate the effectiveness and cost-effectiveness of the STEADI assessment when pragmatically implemented through telemedicine.

## Methods

### Study Design

The STEADI Options RQIT was implemented in 5 primary care clinics between September 1, 2020, and December 31, 2021. The RQIT used a randomized design to compare patients at risk for falls who were assigned to receive a one-time telemedicine fall prevention assessment to a control group of patients at risk for falls who received the standard of care (SOC) of general disease state management. Due to the COVID-19 pandemic, screening was conducted through SMS text messaging–initiated surveys and phone calls, and we adapted the STEADI fall assessment to be implemented through phone- or video-supported telemedicine encounters conducted by a designated RN. Primary care providers were sent assessment information that they could access during the patient’s scheduled visit. We collected patient-level data on recruitment, assessments, health service use, prescriptions, fall events, implementation costs, and all-cause outpatient and inpatient costs incurred over one year using administrative and electronic health records (EHRs) and patient surveys. The following sections describe the study’s implementation and procedures (Figure 1).

The STEADI Options RQIT was a quality improvement initiative supported by health system leadership. Team members obtained verbal consent from study participants to share contact information with an evaluation partner outside the institution for the purpose of surveying (National Opinion Research Center [NORC] at the University of Chicago). Willingness to participate in the evaluation phase did not impact whether the patient received the STEADI evaluation as part of the quality improvement program.

**Figure 1 figure1:**
[figure not shown]
Clinical workflow of the Stopping Elderly Accidents, Deaths, and Injuries (STEADI) Options Trial: recruitment, screening, STEADI assessment, and intervention recommendation (Emory Health Services, 2020-2021). Those who screened at risk for falls but were assigned to the standard of care arm did not complete steps 5, 6, and 8. CRI: clinical research interviewers; RN: research nurses.

### Ethical Considerations

The study protocol was reviewed and approved by the US Office of Management and Budget to assure its compliance with the Paperwork Reduction Act (Office of Management and Budget control number, 0920-1281). Evaluation aspects of the RQIT deemed to be human subjects research (patient surveys) were reviewed by the Emory Institutional Review Board to assure the safety and ethical treatment of human subjects (00111996), and the RQIT was registered (ClinicalTrials.gov NCT05390736).

### Study Setting and Staffing

We selected 5 primary care clinics based on the willingness of clinic leadership to participate, clinic patient population diversity, and the number of older adults served. The research team included representatives from CDC’s Division of Injury Prevention, NORC at the University of Chicago, and the Emory School of Medicine and Emory Healthcare primary care clinicians and staff. The Division of Injury Prevention was responsible for project oversight and fall prevention expertise, NORC designed the study protocol and data collection instruments and managed the project, and Emory was responsible for clinical implementation. Emory hired clinical research interviewers (CRIs), a clinical research coordinator, and RNs to conduct recruitment, coordination, and assessments. CRIs were responsible for screening patients for fall risk, recruiting and enrolling those at risk, scheduling STEADI assessments, and conducting preassessment coordination calls. The clinical research coordinator managed the workloads of the CRIs. The RN was responsible for conducting assessments, providing patient education, creating recommendations based on assessment information, and disseminating those recommendations to the patient's provider. Providers were responsible for determining whether to act on recommendations through the creation of clinical referrals to services or by managing medications. Emory implementation staff participated in monthly calls with the research team to discuss recruitment and implementation. Emory additionally convened monthly meetings between Emory implementation staff and primary care clinic staff to communicate the study design, intent, and responsibilities.

### Information Technology Infrastructure

Before the implementation, Emory integrated the SIS into Tonic (Tonic Solutions), an electronic platform used to administer previsit screening. Through Tonic, patients were able to take the SIS on a web-based device before their appointment using a phone, tablet, or computer, with the results automatically populating the patients’ EHR. The research team used REDCap (Research Electronic Data Capture; Vanderbilt University), a secure, internally hosted web-based application, to capture STEADI assessment results. The RN sent conclusions and recommendations to the provider using the EHR messaging center.

### Study Eligibility

Patients aged 65 years or older with a nonacute outpatient visit scheduled at participating primary care clinics were eligible for screening. Patients completed the SIS, and those with an SIS score of 4 or higher or those who answered “Yes” to any of the statements used as proxy to the 3 key questions within the SIS were eligible for enrollment (Textbox 1) [9]. Patients needed to be cognitively able to participate in the assessment, be able to converse in English, and have access to an able-bodied person to help with or respond to an emergency during the STEADI gait and balance assessments conducted by telemedicine (Textbox 1). Patients without valid phone numbers and those who opted out of receiving health system text messaging were excluded.

Stopping Elderly Accidents, Deaths, and Injuries (STEADI) Options trial patient eligibility criteria, Emory Health Services, 2020-2021.
**Patients aged 65 years or older with a qualifying (ie, nonacute) visit scheduled at 1 of the 5 designated Emory clinic implementation sites and:**
Identified as high risk for falls through the Stay Independent screener by scoring 4 or more or answering affirmatively to any of the following statements in the Stay Independent screener as proxy to the 3 key questions:Sometimes I feel unsteady when I am walking.I am worried about falling.I have fallen in the past year.Able to participate in the STEADI assessments:Cognitively able to answer screening questions and participate in assessment.English-speaking.Have a computer, tablet, phone with internet and a webcam, or telephone.Have an able-bodied helper who can be available to help or called for help during the STEADI gait and balance assessment (in case of unsteadiness or a fall).

### Randomization

Providers were randomized each week 1:1 to either the STEADI or SOC arms based on a dice roll, and their scheduled patients were assigned to study arms based on the provider’s assignment. Providers were rerandomized each week; however, patient assignment remained the same even if they rescheduled an appointment to another week. During 3 weeks in the summer of 2021 when the RN was unavailable, all providers and their patients were assigned to the SOC arm. Over the subsequent 6 weeks, providers and their patients were assigned to the STEADI arm on a 2:1 basis to restore assignment balance, after which the study returned to 1:1 assignment. A total of 2 additional study arms with modified STEADI assessments were discontinued early in the study due to low overall enrollment.

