### Evaluation

We will analyze process outcomes, short- and long-term outcomes, costs, and cost-effectiveness of the implementation (Multimedia Appendix 6). Process analyses will evaluate the extent to which assessments were conducted through phone or Zoom calls, evaluated intended risk factors, and identified risks among participants who were assessed. Qualitative interviews with providers will be thematically analyzed to provide details on whether the intervention was implemented as intended and provide additional information on intervention feasibility, communication between implementation staff, perceived efficacy, and patient engagement.

Using an intent-to-treat approach, we will evaluate sample balance and assess short- and long-term outcomes comparing the STEADI and SOC arms. We will use survey and EHR data to evaluate differences between the arms in the short-term outcomes of (1) STEADI-indicated service use (eg, physical therapy and occupational therapy) and (2) prescriptions for medications that increase fall risks. For the long-term outcomes of (1) medically treated and self-reported falls and (2) all-cause health care costs from the Emory Healthcare system, we will use EHR data and administrative cost data. We will use the *International Classification Definition, 10th Revision, Clinical Modification* (ICD-10-CM) codes (Multimedia Appendix 2) and chart text notes to identify medically treated falls at Emory. Preliminary analyses indicate that ICD-10-CM codes without text note review are insufficient to differentiate individual fall episodes or determine fall severity. Therefore, we will also use self-report of falling with treatment at Emory to guide additional text note reviews for fall events that may not have been coded in the EHR. Falls will be coded as EHR-confirmed, self-reported medically treated falls outside the Emory system (EHR not confirmed), and self-reported and not medically treated to support analyses. We will additionally evaluate the impact of STEADI using a per protocol approach using a 2-stage residual inclusion approach.

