## Results

From September 1, 2020, to December 31, 2021, the study enrolled 720 patients, of whom 307 (42.6%) were assigned to the STEADI arm, 353 (49%) were assigned to the SOC arm, and 60 (8.3%) were assigned to arms that were discontinued. Process and implementation cost data were collected. Follow-up data collection was completed in January 2023. As of February 2024, data analysis is complete, and results are expected to be published in the end of 2025.

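### Patients from three SOC-only weeks were not randomized, yet the article describes all patients as randomized and shows no allowance for the changing allocation probability

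*Protocol article*

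**What the plan says.** The Randomization section of the protocol article sets the base rule: "Providers were randomized each week 1:1 to either the STEADI or SOC arms based on a dice roll", with patients taking the arm of their scheduled provider. It then describes a departure: "During 3 weeks in the summer of 2021 when the RN was unavailable, all providers and their patients were assigned to the SOC arm". The repair was: "Over the subsequent 6 weeks, providers and their patients were assigned to the STEADI arm on a 2:1 basis to restore assignment balance". Once those six weeks were over, the equal ratio was resumed.

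The Abstract (Methods) says, without exception, that all eligible patients were randomized before screening.

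The Evaluation section plans one comparison: "Using an intent-to-treat approach, we will evaluate sample balance and assess short- and long-term outcomes comparing the STEADI and SOC arms". Statistical Procedures adds prespecified multivariable models that control for unbalanced covariates, which are not named, and uses treatment assignment as the instrument for the per-protocol estimate. Neither section mentions allocation period or calendar time. Limitations discusses contamination from weekly provider randomization but not the SOC-only weeks.

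**The concern.** In the SOC-only weeks assignment was fixed by nurse availability, so the probability of STEADI was 0. In the next six weeks it was 2/3, and otherwise 1/2 under the stated 1:1 rule. An unequal ratio does no harm within a period. A contrast pooled over periods with different ratios links arm to enrolment date, and any outcome difference between periods can then leak into the arm effect. The SOC-only patients are compared entirely with STEADI patients from other weeks.

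The article itself describes factors that depend on calendar time:

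- pandemic conditions that may have affected care-seeking, use of preventive services and medically treated falls (Limitations);
- a change in survey incentive after 13 months, so that response could depend on enrolment date (Data Collection);
- a change of EHR vendor that lost about six weeks of follow-up for 80 patients (Limitations, which says the models adjust for it).

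The instrument analysis is exposed too. It relies on assignment being as good as random, and in the SOC-only weeks assignment was determined by the date. Falls, service use and costs are all compared between these arms.

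**Working it through.** **1. The plan's own power figures.** Inputs from Sample Size Estimation: control risk p1 = 0.5, design effect 1.05, p2 = 0.5 × RR. The significance level is not stated, so two-sided 5% is assumed. With n' = n/1.05 per arm, d = p1 − p2 and p̄ the mean risk:

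power = Φ{[d√n' − 1.96√(2p̄(1−p̄))] / √(p1(1−p1) + p2(1−p2))}

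| n per arm | RR | Stated power | Computed power |
|---|---|---|---|
| 500 | 0.82 | 80% | 79.7% |
| 350 | 0.78 | 80% | 81.7% |
| 250 | 0.75 | 80% | 78.7% |

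The stated figures reproduce to within 2 points, so the same method is used in step 5.

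**2. Patients affected.** Results gives the window and the counts: "From September 1, 2020, to December 31, 2021, the study enrolled 720 patients", of whom "307 (42.6%) were assigned to the STEADI arm" and "353 (49%) were assigned to the SOC arm".

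- Window: 487 days / 7 = 69.6 weeks.
- STEADI plus SOC: 307 + 353 = 660, and 660 / 69.6 = 9.5 per week if enrolment was even (assumption).
- SOC-only weeks: 3 × 9.49 = 28.5, about 28 patients, and 28.5 / 353 = 8.1% of the SOC arm.

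**3. Net effect of the 3 + 6 weeks.** Let w be the weekly load, taken as constant.

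| Period | STEADI | SOC |
|---|---|---|
| 3 SOC-only weeks | 0 | 3w |
| 6 weeks at 2:1 | 6 × 2/3 = 4w | 6 × 1/3 = 2w |
| Total | 4w | 5w |

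The deficit is 3w. The six weeks recover 4w − 2w = 2w, which is two thirds of it. At w = 9.5 the episode gives about 38 STEADI and 47 SOC. Full recovery would need nine weeks at 2:1 (3 ÷ 1/3), or 3:1 over six weeks (a STEADI share of 4.5/6), or weekly enrolment in the catch-up weeks 1.5 times that of the SOC-only weeks.

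**4. Size of the bias.** Suppose there is no treatment effect and fall risk is 0.50 except in the SOC-only weeks. The pooled SOC risk is 0.50 + (r − 0.50) × 0.0806, where r is the risk in those weeks.

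| r | SOC risk | Apparent RR |
|---|---|---|
| 0.35 | 0.488 | 1.025 |
| 0.40 | 0.492 | 1.016 |
| 0.60 | 0.508 | 0.984 |
| 0.65 | 0.512 | 0.976 |

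The values of r are illustrative; the article gives no risk by period.

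**5. Cost of removing the three weeks.** SOC falls from 353 to about 325 and STEADI stays at 307. With the method of step 1 adapted to unequal arms, power at RR 0.78 goes from 79.2% to 77.6%, and at RR 0.75 from 88.5% to 87.2%. The RR detectable with 80% power moves from 0.778 to 0.773.

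**The case against.** **The effect is small.** The departure was caused by staffing, not patient prognosis, so calendar time is the only evident route to bias. Follow-up lasts 365 days, so any two patients enrolled within the nine-week episode share at least 365 − 63 = 302 days. If a 10-point shift applied equally to all nine weeks, the 2:1 phase would largely offset it and the null RR would be about 0.998 or 1.002. This stands as a limit on size. It does not settle the matter: the pooled contrast also uses STEADI patients enrolled up to a year earlier, whose follow-up overlaps far less, and nothing shows that the shift was common to all nine weeks.

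**The SAP may handle it.** A reader might infer that no model term or exclusion deals with these weeks. The documents cannot support that: the covariate list is not given, and neither an SAP nor the evaluation-design appendix is shown. What remains is that the article describes a pooled analysis, calls all patients randomized, and leaves the episode out of its Limitations.

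**The balance statement expresses a purpose.** A reader might infer that the repair was simply wrong and that nine weeks were required. That holds only with equal weekly enrolment. Nor does the episode explain the final gap of 353 − 307 = 46; the residual of about 9.5 is roughly a fifth of it.

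**Other inferences go too far.** The two discontinued arms do not by themselves tie STEADI versus SOC to calendar time, because the article states 1:1 between these two and gives no different early ratio. It says only that care-seeking may have been affected, not that it changed.

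**Excluding patients now would be post hoc.** Analysis was complete by February 2024, so dropping assigned patients departs from the stated intent-to-treat approach. This is a fair reason to prefer stratification, which keeps every patient in the assigned arm, and to report the pooled result beside it.

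**Conclusion.** The point holds at moderate severity. Three weeks of SOC patients were allocated deterministically, the Abstract's statement is too broad for them, and the analysis as described does not reflect an allocation probability that moved from 1/2 to 0 to 2/3 and back. Equal head counts would not cure this, because they do not supply the missing concurrent comparator.

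On even accrual about 28 SOC patients (8% of the arm) are involved. The apparent RR under no effect stays between about 0.976 and 1.025 for shifts of up to 15 points in fall risk. A reader might infer that the randomized comparison is invalid or that the trial cannot be interpreted without this change. The figures do not support that: 10-point shifts move the SOC risk by about 0.8 points, against a detectable difference of about 0.5 × (1 − 0.778) = 11 points. The fall calculation does not carry over to service use or costs, for which the article gives no figures to work from.

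**What to change.** - Stratify or adjust every STEADI versus SOC model for allocation period: 1:1, SOC-only, 2:1, final 1:1. Include the same terms in both stages of the instrument analysis. With full stratification the SOC-only weeks contribute no arm contrast, so separate exclusion is unnecessary. Excluding those weeks is the simpler alternative.
- Report the all-patient pooled result as a sensitivity analysis, and say that the period handling was added after the analysis was completed if that is so.
- Qualify the Abstract's statement that all eligible patients were randomized, and list the three weeks under Limitations.
- Describe the 2:1 period as intended to reduce the imbalance, and give the enrolled counts by arm and period so that the even-accrual assumption can be dropped.

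The cost is a few period indicators built from enrolment dates already held, a rerun of the models, some rewording, and the small loss of precision in step 5 of the working.
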